## Abstract

Stroke is a leading cause of long-term disability, with more than half of survivors experiencing persistent upper limb impairments. Despite clear evidence that high-dose, repetitive, task-specific training is essential for motor recovery, many stroke survivors do not receive a sufficiently high therapy dose – particularly in the outpatient phase. Limited therapist availability, high care costs, and travel burdens remain key barriers to accessing rehabilitation training. While technology-assisted rehabilitation has emerged as a promising solution, most existing studies are limited to single-device interventions, are conducted in clinical settings, and/or require constant supervision, thereby restricting their scalability and impact. This study protocol presents the Technology-Assisted Rehabilitation Gym for at-home Training (TARGeT) trial (ClinicalTrials.gov: NCT06406569), which aims to evaluate the feasibility, safety, usability, clinical benefits, and economic potential of a novel, unsupervised, high-dose home-based therapy program that integrates multiple complementary technologies for upper limb stroke rehabilitation. In this single-centre, pilot feasibility trial, up to 30 subacute and chronic stroke survivors will complete six weeks of daily home-based therapy using three complementary rehabilitation technologies that enable self-administered training without therapist supervision. The training will be remotely monitored by clinicians via an online platform that reports data on the training progress. Assessments will be conducted at five timepoints, measuring clinical outcomes (e.g., FMA, ARAT), quality of life, healthcare utilization, and technologies’ perceived usability (SUS, RawTLX). The study will assess whether unsupervised, home-based multi-technology rehabilitation is feasible and safe, provides high usability and satisfying user experience, whether it yields clinical outcomes comparable to conventional therapy based on data from previous studies (own data and literature data), and determines the associated costs relative to conventional therapy. The TARGeT program addresses the critical gap in therapy access and intensity by delivering scalable, high-dose rehabilitation directly into patients’ homes. Results will inform future trials and support broader adoption of decentralized, technology-enabled stroke rehabilitation.

## Introduction

Stroke is a leading cause of long-term disability, with approximately 50% of stroke survivors suffering from upper limb impairments [1,2]. To diminish sensorimotor impairments, stroke survivors can undergo physical rehabilitation and maintenance programs in hospitals or rehabilitation centres. Current evidence in stroke rehabilitation emphasizes the need for repetitive and intensive task-specific upper-extremity training to facilitate motor relearning and neuroplasticity [3]. While physical therapy aims to decrease functional dependence, care costs and burden on caregivers, and provide a higher quality of life [4], there is growing evidence that the therapy dose received by stroke survivors along the continuum of care is insufficient. This is especially prevalent in the (later) outpatient phase [5–7].

Changing demographics in many industrialized countries will increase the number of patients requiring neurorehabilitation further over the next years. An increased number of patients leads to a rising demand for healthcare professionals and a high burden on healthcare costs. Providing access to adequate doses of rehabilitation poses a significant challenge due to linked manpower shortages and high associated costs. Technological solutions, such as rehabilitation robotics, hold the promise to complement traditional therapy in cost-effective ways, especially if used without constant supervision from trained personnel. Upper limb technology-assisted therapy can provide task-specific, intensive, and repetitive exercises with comparative results in terms of impairment reduction and functional improvement as conventional therapy [8]. Complementing traditional one-on-one treatment with a therapist by technology can help decrease manpower requirements and therein, costs since minimal or no supervision is required [9,10].

While most of these technologies typically focus on one specific segment of the body, in recent studies, it has been proposed to combine several technologies to set up a circuit or gym training in the clinic that allows for more holistic training as typically present in post-stroke technology-aided neurorehabilitation [e.g., 11–14]. Bustamante et al. [11] showed that stroke survivors who underwent circuit training with six different devices according to a pre-defined time per station yielded descriptively similar clinical gains as those who received time-matched conventional care (each n = 10). The circuit training also proved to be more cost-effective due to the reduced supervision ratio of the therapists of 1:6 compared to 1:1 in the standard care group. Similarly, a multicenter clinical trial compared the time-matched training with four robotic devices to conventional therapy and could achieve comparable results across the treatment groups regarding the Fugl-Meyer Assessment (FMA) score [12].

Besides the limited availability of trained therapists, the challenge of receiving a sufficiently high therapy dose further aggravates as stroke survivors progress in their rehabilitation journey. In Singapore, it has been shown that rehabilitation adherence falls to 20% after three months of stroke onset, 10% after six months, and 4% after one year, with travel inconveniences, stroke survivors’ wish not to burden caregivers and high cost being the main reported barriers [15]. Tapping the full potential of technology-aided solutions would include adapting treatment and selection protocols, technology and monitoring systems to be directly accessible in the homes of stroke survivors [16]. Home-based technology-aided rehabilitation immediately reduces traveling burdens and associated costs, and has the potential to lower therapy costs due to the reduced demand for clinical resources. Additionally, training at home can lessen caregiver involvement if technologies with high usability are used, and can, thus, be used without continuous supervision from therapists. It further allows to distribute the training over a day as per one’s convenience which might reduce fatigue and enhance compliance [17]. Aguirre-Ollinger et al. [18] showed in a recent study that technology-aided therapy at home could be more cost-effective than clinic-based conventional therapy. Similarly, several other studies revealed favorable economic outcomes for home-based technology-aided therapy [19,20], whereby the cost reduction was achieved by eliminating therapist supervision and minimizing travel expenses. Moreover, the first studies that employed single devices at stroke survivors’ homes for unsupervised therapy have shown that adherence to the therapy program is high and that functional outcomes could be improved, e.g., in [18,21–24]. Yet, these studies included only one device, hence, focused on one specific aspect of therapy. As a result, they may only be suitable for patients with certain levels of impairment and may not be adaptable to the changing needs of stroke survivors along their rehabilitation journey.

To address the increasing demand for comprehensive, high-dose therapy we aim to bring home-based technology-aided rehabilitation even further by combining the benefits of a robotic gym with home-based therapy. We propose to deploy three complementary rehabilitation technologies, each focusing on a different part of the upper limb, subsequently at stroke survivors’ homes. The technologies allow for comprehensive training, including sensory, motor, and cognitive aspects, while therapists can monitor the training progress remotely from the clinic. Specifically, these technologies are highly usable and allow for individualized therapy programs depending on the specific upper limb impairment and the changes therein over the course of rehabilitation (i.e., focus on proximal or distal parts), while drastically increasing upper limb practice intensity and duration compared to usual clinic frequencies while reducing the requirements for clinical manpower, caregiver, and travel expenses, leading to a potentially economically effective rehabilitation model.

In the following, we present the study protocol for the Technology-Assisted Rehabilitation Gym for at-home Training (TARGeT) feasibility study in which up to 30 subacute and chronic stroke survivors will undergo six weeks of unsupervised, self-administered upper limb therapy at home. Specifically, we designed this study protocol to i) investigate whether unsupervised, home-based therapy with a set of complementary rehabilitative technologies is feasible and safe for stroke survivors, ii) assess the usability and user experience of stroke survivors and therapists with respect to the proposed TARGeT program, iii) evaluate whether a clinical benefit comparable to conventional therapy as reported in [9] can be achieved, and iv) to perform an economic analysis with respect to conventional therapy with data of previous studies [18]. The outcomes of the study will inform whether the TARGeT program is a feasible, safe, and economical way to tackle the increasing demand for post-stroke upper limb neurorehabilitation.

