## Methods and analysis

### Study design, setting and participants

The study design is a clinical, single-group, open-label, pilot feasibility trial to evaluate the concept of a novel therapy concept, TARGeT program, in which three complementary neurorehabilitation technologies targeting different segments of the upper limb are deployed at stroke survivors’ homes in Singapore (Fig 1). Participants will undergo six weeks of intensive at-home therapy successively using these technologies according to tailored therapy plans while the training progress is remotely monitored by clinicians. The study will be conducted in the rehabilitation outpatient clinic of Tan Tock Seng Hospital, Clinic for Advanced Rehabilitation Therapeutics, National Healthcare Group (NHG) and in participants’ homes.

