**Fig 1 pone.0355160.g001:**
[figure not shown]
TARGeT intervention: Protocol and procedures. The protocol consists of a preparation phase in the hospital (assessments, device onboarding), a 6-week home-based intervention where participants train using the technologies, and a follow-up phase in the clinic to assess the effects of the intervention. A) Schematic participant timeline according to the SPIRIT reporting guidelines, B) illustrative protocol overview.

Ethical approvals were obtained from the NHG Domain Specific Review Boards on 13 June 2024 (ECOS reference number: 2023/00527, protocol version 2, see S2 File) and ETH Zurich Ethic Commission on 11 March 2024 (Reference number: 23 ETHICS-342). The study will be conducted according to the Declaration of Helsinki and all participants will provide signed written informed consent to the clinical team before participation. The study was registered on ClinicalTrials.gov with the following registration number: NCT06406569 on 06 May 2024. Additionally, for personal data protection and cybersecurity, approval from Singapore’s national health tech agency, Synapxe, was obtained before the commencement of the study. Results of the study will be made available in scientific publications.

This manuscript was written in accordance with the SPIRIT (Standard Protocol Items: Recommendations for Interventional Trials) guidelines [25] (see S1 File).

With reference to pilot studies, sample sizes in the range of 10–30 participants are recommended [26]. We will therefore recruit up to 30 participants, aiming for a sample size of 25, factoring in a drop-out rate of about 20% (5 participants).

The inclusion and exclusion criteria for participants were derived from experiences in previous studies with the technologies used here [9,18,27,28].

The inclusion criteria are as follows:

Clinical stroke (ischaemic or haemorrhagic) confirmed by admitting doctors and brain imaging (computed tomography (CT), CT angiography or magnetic resonance imaging)Age 21–80 yearsAt least 28 days post-strokeUpper limb motor impairment of FMA scale [29] 20–60Montreal Cognitive Assessment (MoCA) [30] > 21/30Ability to sit supported and continuously for 60 minutesStable home abode with enough space to place technologies (clear floor area of at least 1.2m x 2.0m in the proximity of a power socket)Availability of caregiver to assist in home-based exercises

Participants will not be recruited if any of the following exclusion criteria are present:

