To evaluate the clinical impact of the TARGeT program, a two-way repeated measures analysis of variance (ANOVA) will be conducted for each clinical scale *time point* and *intervention group* as factors. The *time point* factor (pre, mid, post, follow-up 1, follow-up 2) is intended to assess both the immediate effects of the intervention and the long-term retention of the treatment gains. We hypothesize that motor function as assessed by ARAT etc. will improve significantly during the intervention period and that these gains will be maintained at follow-up. The *intervention group* factor (TARGeT intervention, conventional therapy) will compare the effects of the TARGeT intervention on clinical scales with duration-matched conventional therapy data from previous studies and the literature [9]. In addition, the interaction between *time point* and *intervention group* will be examined to determine whether temporal changes differ between groups. We hypothesize that the clinical impact (FMA, etc.) of the TARGeT program will be comparable to that of conventional therapy, validating the program as an effective technological alternative to traditional rehabilitative methods. Any additional health benefit in terms of quality of life will be determined by descriptive analysis of the SS-QoL and EQ-5D scales. Note that if the data violates the assumptions for parametric testing (normality – Shapiro-Wilk test, homogeneity of variance – Levene’s test), we will instead utilize the non-parametric test for these comparisons (e.g., Aligned Rank Transform ANOVA).

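### The conventional-therapy comparator is described inconsistently and not fixed, and the planned ANOVA makes no allowance for differences between studies

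*Protocol article*

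**What the plan says.** The comparator is described in three places in the protocol article.

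- Introduction, objective iii: the aim is to "evaluate whether a clinical benefit comparable to conventional therapy as reported in [9] can be achieved". This is one cited source.
- Abstract: clinical outcomes are to be "comparable to conventional therapy based on data from previous studies (own data and literature data". This is at least two kinds of source.
- Data analysis: the comparison is with "duration-matched conventional therapy data from previous studies and the literature [9". The wording is plural, but [9] is the only reference given.

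On the model, Data analysis states that "a two-way repeated measures analysis of variance (ANOVA) will be conducted for each clinical scale", with time point and intervention group as factors. The group "factor (TARGeT intervention, conventional therapy) will compare the effects of the TARGeT intervention on clinical scales", and the interaction of group with time "will be examined to determine whether temporal changes differ between groups". No study or source component is mentioned. The rank-based fallback is offered for the same comparisons.

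On design, "The study design is a clinical, single-group, open-label, pilot feasibility trial". Status and timeline gives data collection from 12 August 2024 to 05 June 2026, with complete analyses afterwards. The article gives no list of comparator datasets, no selection rule and no date by which the set is closed.

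**The concern.** There are two separate issues.

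First, a reader cannot tell which data form the control group. With no concurrent control arm, the choice of external data determines the comparison. TARGeT scores are open to the team as they accrue, and Data analysis says that comparability with conventional therapy would validate the program. A comparator left open under these conditions can be settled after the results are known, and the reader could not tell whether that had happened.

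Second, every TARGeT participant comes from one study and every comparator participant from another, so group and study cannot be separated. Differences between studies in raters, calendar time, setting and case mix enter the group contrast, but the ANOVA error term contains only variation between and within participants. Any p-value or interval for the group-by-time contrast therefore treats between-study variation as zero. What is at stake is how firmly aim iii can be reported.

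**Working it through.** **Inputs from the documents.** The only sample-size figure is to "recruit up to 30 participants, aiming for a sample size of 25, factoring in a drop-out rate of about 20% (5 participants". It reproduces as 25 × 1.2 = 30 (5/25 = 20%, 5/30 = 16.7%). The point does not depend on it beyond supplying 25 for the TARGeT group.

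**Inputs assumed.** The documents give no SD of change, comparator size or between-study SD. For illustration: SD of FMA gain 6, 25 comparator participants, and study mean gains varying with SD tau = 0, 1, 2 or 3 points. A single contrast of change between two time points is used; for two time points the group-by-time interaction is the two-sample comparison of change.

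**Step 1, what the ANOVA counts.** SE_within = 6 × √(1/25 + 1/25) = 1.70. The nominal 95% half-width is 1.96 × 1.70 = 3.3 points.

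**Step 2, allowing for study.** With K equally weighted comparator studies, SE² = SE_within² + tau²(1 + 1/K), where SE_within² = 2.88. For K = 1 the added term is 2·tau². Coverage of the nominal interval is P(|Z| < 1.96 × 1.70 / SE).

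| tau | SE, K = 1 | Half-width, K = 1 | Coverage of nominal 95% interval, K = 1 | Half-width, K = 3 (same total of 25) |
|---|---|---|---|---|
| 0 | 1.70 | 3.3 | 95% | 3.3 |
| 1 | √(2.88 + 2) = 2.21 | 4.3 | 87% | 1.96 × √(2.88 + 1.33) = 4.0 |
| 2 | √(2.88 + 8) = 3.30 | 6.5 | 69% | 1.96 × √(2.88 + 5.33) = 5.6 |
| 3 | √(2.88 + 18) = 4.57 | 9.0 | 53% | 1.96 × √(2.88 + 12) = 7.6 |

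The nominal interval is right at tau = 0 and too narrow for any tau above 0. For a given tau, the shortfall is larger with one comparator study than with three.

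**Step 3, a milder model.** If only the comparator studies vary and TARGeT carries no study effect of its own, the added term is tau²/K. For K = 1 the half-widths are then 1.96 × √(2.88 + 1) = 3.9, 1.96 × √(2.88 + 4) = 5.1 and 1.96 × √(2.88 + 9) = 6.8. The direction is the same and the size smaller.

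**Step 4, simulation.** Two-sample tests on change, with 25 TARGeT participants and three comparator studies of 8, gave error rates of 4.9%, 11.8%, 20.4% and 35.8% at a nominal 5% for tau/SD = 0, 0.2, 0.3 and 0.5. The formula with 25 comparator participants gives 5.0%, 12.9%, 21.5% and 38.9%.

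**Step 5, would a fixed study term help?** With TARGeT and three comparator studies there are four study means. An intercept, a group term and a term for each comparator study make five columns of rank 4. Group is aliased with study, so a fixed study term cannot repair the contrast.

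**The case against.** The wording conflict is narrower than it first appears. Data analysis cites only [9], which the article also lists among earlier studies with these technologies, so that sentence could describe one published study. It also restricts the comparator to duration-matched data. Both points stand, but the restriction narrows the set without closing it, and the Abstract's pairing of own and literature data is hard to read as one study.

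The full protocol (S2 File) and any analysis plan are not shown and may name the dataset. If so, the repair is to carry that name into the article; its statements would still need aligning.

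The aim is secondary. The primary outcomes are technology data and the journal and report forms, and the Discussion already asks for caution about comparability because there is no randomised control. This lowers the weight of the point. The caveat does not, however, settle which data are used or change the stated test.

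Four stronger readings are tempting, and the documents do not support them.

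- A reader might infer that pooling several sources causes the narrowing. It does not: for a given tau, a single source is worse.
- A reader might infer that either issue could reverse the trial's conclusion. No margin or decision rule is stated, so there is no defined conclusion to reverse.
- A reader might infer that between-study variation is the dominant uncertainty. Tau is unknown, and at tau = 1 with one study per side its contribution (2.0) is below the within-study variance (2.88).
- A reader might infer that a comparator has been or will be picked to suit. The text shows only that the choice is open. Quantifying selection would need the number of candidate sources and the way they are chosen, neither of which is given.

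**Conclusion.** The point holds in two parts. The article describes the comparator inconsistently and does not fix it, in an open-label trial where the external data are the entire control arm. Independently, the stated ANOVA confounds group with study, so its p-values and intervals for TARGeT against conventional therapy reflect participant variation only.

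The first part rests on the text alone. The size of the second is conditional. On the illustrative inputs with one study per side, a half-width of 3.3 points should be 4.3 to 9.0 for tau from 1 to 3, and nominal 95% coverage is 87% down to 53%. It would be correct at tau = 0, and the documents cannot say where in that range the trial lies. For a secondary aim of a pilot, this is a change that should be made, not one that undermines the study.

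**What to change.** Align the Abstract, objective iii and Data analysis by naming one primary comparator dataset now, before the complete analyses. The conventional arm of [9] would match objective iii. Label any other own or literature source as sensitivity. Because collection began on 12 August 2024, record the date of the decision and which TARGeT results had been seen by then; naming the dataset now limits later choice but cannot undo earlier sight of the data.

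Report the TARGeT-minus-conventional difference in change with an interval. Add a sensitivity table for tau = 0, 1, 2 and 3 points using SE² = SE_within² + tau²(1 + 1/K), with SE_within taken from the actual data. A single source gives the largest added term for a given tau, which is why the table belongs with this choice: naming one dataset removes the freedom to choose, and the table shows the uncertainty that remains. Do not rely on a fixed study term, which is aliased with group, or on a tau estimated from only a few studies.

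The cost is a few lines of wording, one extra table and wider intervals against conventional therapy. No further data need be collected from TARGeT participants.

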## Methods and analysis

### Study design, setting and participants

The study design is a clinical, single-group, open-label, pilot feasibility trial to evaluate the concept of a novel therapy concept, TARGeT program, in which three complementary neurorehabilitation technologies targeting different segments of the upper limb are deployed at stroke survivors’ homes in Singapore (Fig 1). Participants will undergo six weeks of intensive at-home therapy successively using these technologies according to tailored therapy plans while the training progress is remotely monitored by clinicians. The study will be conducted in the rehabilitation outpatient clinic of Tan Tock Seng Hospital, Clinic for Advanced Rehabilitation Therapeutics, National Healthcare Group (NHG) and in participants’ homes.

